### Participant timeline {13}

Table 3 summarises the participant timeline including the assessments at each visit.

**Table 3 Tab3:** Visit schedule and assessments

	**Screening** **(Baseline day)** **−28–0**	**Visit 1** **Rando** **Day 0**	**Visit 2 ****Intervention** **Day ****1–7** after Rando (only TIPS group)	**Visit 3 ****Discharge ****4 days** after intervention** (+ 7/−2 days) **(only TIPS group))	**Visit 4 ****M1 ****1 month **after Rando **(+ 2 weeks)**	**Visit 5 ****M3 ****3 months **after Rando **(± 4 weeks)**	**Visit 6 ****M6 ****6 months **after Rando **(± 4 weeks)**	**Visit 7 ****M9 ****9 months **after Rando **(± 4 weeks)**	**Visit 8 ****M12** **12 months** after Rando **(± 4 weeks)**	**FU ****Every 6 Month until EOS***^**2**^
Informed Consent	x									
Registration (i.e. entry of first data in eCRF)	x									
Inclusion-/Exclusion criteria	x									
Randomisation		x								
Demographics	x									
Medical history	x									
Physical examination, vital signs	x									
Pregnancy test	x									
12-lead ECG	x									
Colour Doppler ultrasound	x			x	x	x	x	x	x	
Echocardiography (TTE)	x						x			
TIPS (according randomisation)			x							
Laboratory (haematology, clinical chemistry, coagulation)	x**		**:	x	x	x	x	x	x	
Urinalysis	x						x			
Clinical scores^1^	x			x^1^	x^1^	x^1^	x^1^	x^1^	x^1^	
Paracentesis	(x)									
SF-36, CLDQ	x						x		x	
Survival status, liver transplantation				x	x	x	x	x	x	x
Concomitant medication	x	x	x	x	x	x	x	x	x	
(S)AEs	x	x	x	x	x	x	x	x	x	x

*CLDQ *Chronic Liver Disease Questionnaire, *ECG* electrocardiography, *FU* follow up,* Rando* randomisation,* SF-36* Short Form Health Survey (questionnaire)

^*^EOS = end of the entire study is defined as 12 months after randomisation of the last patient

^**^Laboratory tests in screening must be carried out as close as possible to randomisation

(1) Clinical scores include: HE (West Haven Criteria), MELD, MELD Na, MELD 3.0, FIPS, CLIF-C AD, Child-Pugh and NYHA will be documented in eCRF at screening; thereafter, only HE (West Haven Criteria) and NYHA will be collected in eCRF beginning from Visit 3

(2) Only the first paracentesis which is necessary after the study period of 12 months is documented including the date of paracentesis. Further paracenteses after the first one in FU are not considered

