### Plans to promote participant retention and complete follow-up {18b}

In the first year after randomisation, regular and timely visits support patient contact. After the first year, phone calls also promote long-term follow-up.

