SF-36 and CLDQ will be compared between treatment arms at two different timepoints (months 6, 12). At both timepoints, a mixed linear model for repeated measures (MMRM) is used modelling the respective scale at this and the earlier timepoints, and including randomised treatment and the baseline value of the respective subscale and centre as covariates. Two-sided *p* values of the tests of the hypotheses that the treatment effect is zero at the respective timepoints will be calculated from these models. As estimates of the effect sizes, the differences of adjusted means (TIPS arm vs.SMT arm) will be calculated with two-sided 95% CI.

The total number of AEs, the minimum, maximum and mean number of adverse events (AEs) per patient, the total number of follow-up (FU) days (number of days in the observation period), the number of AEs per FU-day (total number of AEs divided by the total by the number of follow-up days), the number of patients who had at least one AE and the number of patients who stopped treatment due to AE will be given.

The probability of AEs defined by preferred term (PT) according to MedDRA and of AEs defined by system organ class (SOC) according to MedDRA will be estimated by the Aalen-Johansen estimator. For this purpose, the time from randomisation to the first occurrence of the specific type of AE (defined by PT or defined by SOC) will be analysed. For patients not experiencing the specific type of AE, the time to the end of the documentation period or death, whatever occurs first, will enter the analysis and will be treated as a competing event. This will result in probability estimates (cumulative incidences) for the different AE types (defined by PT and by SOC) over time. The results will be displayed in summary tables by showing the cumulative incidences at the maximum observation time. Incidences of AEs will be calculated with 95% confidence intervals. Additionally, the number of non-serious AEs will be summarised by PT and by SOC.

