### Adverse event reporting and harms {22}

An adverse event (AE) in this study is defined as any untoward medical occurrence/complication in a patient who underwent TIPS or received SMT and which does not necessarily have to have a causal relationship with the TIPS implantation or received therapy.

Table 5 summarises the parameter/adverse events that will be documented to monitor interventional and SMT safety.

**Table 5 Tab5:** Parameter/adverse events that will be documented to monitor interventional and SMT safety

**During TIPS procedure**	**After the end of the procedure AEs related to TIPS implantation**	**For all patients **
• Injury to carotid artery (perforation) • Procedural pneumothorax • Injury to hepatic artery (perforation/puncture) • Liver capsule perforation • Bile duct injury • Arrhythmia • Allergic reaction • Injury to surrounding organs • Intra-abdominal bleeding • Other	• Complications related to the shunt: – TIPS thrombosis – TIPS dysfunction • Contrast media toxicity • Fistula formation • Other directly related to TIPS procedure	• Bleeding oesophageal varices • Hepatic encephalopathy (HE) beginning from grade II [25] • Spontaneous bacterial peritonitis (SBP) • HRS-AKI • Acute kidney injury (AKI) • Acute on chronic liver failure (ACLF) • Diuretic-induced complications • Cardiac failure (according to NYHA class) • Ischemic hepatitis • Infections • Hepatocellular carcinoma (HCC) (including at least BCLC staging, tumor diameter, vascular invasion etc.) • Other

Adverse events have to be documented in the eCRF starting from the date of ICF signature and until end of the study with the following information: characterisation of the event (listed complication, see above [diagnosis or symptoms, if diagnosis not yet available]), onset/end date, severity according to the current version of CTCAEv5, relationship to procedure (yes/no) or to the shunt (yes/no), serious/non-serious and outcome.

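### The single AE rate per follow-up day mixes a closely monitored first year with a later period without scheduled laboratory, Doppler or HE/NYHA checks; it should be split at month 12

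*Protocol article*

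**What the plan says.** The statistical methods section ({20a}) lists several descriptive safety summaries. One is "the total number of follow-up (FU) days (number of days in the observation period"; another is "the number of AEs per FU-day (total number of AEs divided by the total by the number of follow-up days". No cap at month 12 is stated, the observation period is not dated, and no test, ratio or confidence interval is attached to this rate. The same section also plans Aalen-Johansen cumulative incidences by preferred term and system organ class, with 95% confidence intervals.

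The harms section ({22}) sets the collection window: "Adverse events have to be documented in the eCRF starting from the date of ICF signature and until end of the study". A footnote to Table 3 ({13}) fixes the end: "end of the entire study is defined as 12 months after randomisation of the last patient".

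In Table 3 the rows "Laboratory (haematology, clinical chemistry, coagulation" and "Colour Doppler ultrasound", the clinical scores (West Haven and NYHA from Visit 3 on) and concomitant medication all have their last tick at month 12. The six-monthly follow-up column has only survival/transplantation status and (S)AEs. The retention section ({18b}) adds: "After the first year, phone calls also promote long-term follow-up".

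**The concern.** Days after month 12 count in the denominator exactly like days before it, while scheduled surveillance becomes thinner. Several events listed in Table 5 are recognised largely through the checks that stop: acute kidney injury, HRS-AKI, diuretic-induced sodium and potassium changes, ischaemic hepatitis, TIPS dysfunction or thrombosis, and encephalopathy from grade II. If some of these go unrecorded later on, the pooled figure falls below the first-year rate because monitoring changed, and a reader cannot tell how much of the fall is real.

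The rate matters because the cumulative incidences count first occurrences by AE type. AEs per follow-up day is the only time-adjusted summary of total AE burden, repeat events included.

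**Working it through.** **The plan's own figure.** The article states no AE rate, so there is none to reproduce. The survival inputs can be checked against the stated 57 events. One-year TFS of 66% and 82% gives yearly hazards −ln(0.66) = 0.4155 and −ln(0.82) = 0.1985, ratio 0.4776. The Schoenfeld formula 4(1.960 + 0.842)²/(ln HR)² gives 57.5 events at 0.4776 and 58.3 at the rounded 0.48. Power at 57 events is 79.7% and 79.1%. The inputs agree with the plan to within two events.

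**Inputs.** TFS 66% and 82% (sample size section, {14}); recruitment over 36 months, taken as uniform ({15}); end of study 12 months after the last randomisation (Table 3 footnote). Follow-up is therefore uniform on 1 to 4 years. Assumed here: exponential survival, and TFS as a proxy for time under AE observation.

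**Person-time per patient, h = yearly hazard.**
- First 12 months: D1 = (1 − e^(−h))/h. SMT 0.34/0.4155 = 0.818 years; TIPS 0.18/0.1985 = 0.907 years.
- Total: 1/h − [e^(−h) − e^(−4h)]/(3h²). SMT 1.499 years; TIPS 1.925 years.
- After month 12: D2 = total − D1. SMT 0.680 years, a share of 45%; TIPS 1.018 years, a share of 53%.

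Adding the plan's drop-out rate of 0.01 (taken as per year; no unit is given) leaves the shares at 45.1% and 52.5%.

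**Dilution.** Let q be AE detection after month 12 relative to the first year. With a constant true AE rate, equal in both arms, the pooled rate relative to the first-year rate is (D1 + qD2)/(D1 + D2) = 1 − (1 − q) × share after month 12.

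| q (assumed) | SMT | TIPS | TIPS/SMT |
|---|---|---|---|
| 1 | 1.00 | 1.00 | 1.00 |
| 0.75 | 0.89 | 0.87 | 0.98 |
| 0.5 | 0.77 | 0.74 | 0.95 |
| 0.25 | 0.66 | 0.60 | 0.92 |

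Example: SMT at q = 0.5 is 1 − 0.5 × 0.454 = 0.773, or 23% below the first-year rate. With equal survival and equal q in the two arms, the ratio in the last column is 1.00 at every q.

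**Sensitivity to the end of study.** The sample size section assumes two further years of follow-up after recruitment, not 12 months. The shares then become about 54% and 63% (with drop-out), and the ratio is about 0.975 at q = 0.75 and 0.94 at q = 0.5. The two passages need reconciling, since the denominator depends on which applies.

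**The case against.** The strongest reply is that numerator and denominator cover the same window. Table 3 ticks (S)AEs in the follow-up column and the harms section requires documentation to the end of the study. This stands. A reader might infer that the later days carry no AE collection; that is q = 0, which would put the rates 45% and 53% below the first-year rate with a ratio of 0.86. The documents contradict that case.

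The loss of detection may also be modest. The comparator section ({6b}) puts diuretic treatment under regular renal, sodium and potassium control with no end at month 12. The retention section says that calls also help, not that contact is by telephone only. Bleeding, peritonitis, ACLF or infection can be reported without a study visit. So q is unknown and differs by event type.

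A reader might further infer that the plan makes TIPS look safer. That is not a property of the plan: apart from Visits 2 and 3, the schedule is the same in both arms. A distortion between arms needs longer survival under TIPS or different detection, and even at the design hazard ratio it is 2% to 5% for q = 0.75 to 0.5. The calculation also uses randomised arms, whereas the safety set follows treatment received and SMT patients may receive TIPS. No rate ratio is planned.

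Nor is this the only safety summary that accounts for follow-up time, since the Aalen-Johansen estimates do so too. Finally, the constant-rate model is crude: procedural events cluster in the first days after randomisation, so part of any decline in the TIPS arm is real. That limits the model but is a further reason to show the periods separately. The full protocol or SAP may already date the observation period or split the table.

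**Conclusion.** The point holds as a cheap improvement to a descriptive summary. One pooled rate combines two surveillance intensities, with roughly half of the days (45% SMT, 53% TIPS) in the less intensive period. If detection there is three quarters to one half of the first-year level, the pooled rate is 11% to 23% (SMT) and 13% to 26% (TIPS) below the first-year rate; if detection is unchanged, there is no dilution. The dilution within each arm needs only q below 1. The effect between arms needs a difference in survival or detection as well, and is small.

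These sizes rest on exponential survival at the plan's TFS values, uniform accrual, a constant true AE rate, TFS as a proxy for AE follow-up and an assumed q. If transplanted patients stay under AE observation, the later share is larger.

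**What to change.** In {20a}, or in the SAP if it already carries this detail, date the start and end of the observation period; AE documentation starts at consent, so the start needs stating too. Then report AEs per follow-up day separately for randomisation to the month-12 visit and for month 12 to end of study. Each period takes its own AE count and its own days, and the first serves as the main descriptive comparison. Keep serious and non-serious AEs in both: limiting the later rate to serious events would drop late non-serious shunt dysfunction, although TIPS dysfunction is a named safety outcome.

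The cost is a sentence of wording and one extra table split, with no new data. The main rate uses fewer patient-days. The split does not restore events missed after month 12, and it leaves the cumulative incidences at maximum observation time as they are.

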### Sample size {14}

Sample size calculation is based on the primary endpoint transplantation-free survival (TFS), defined as time from randomisation to liver transplantation or death. It is assumed that the TFS probability of patients in the control group (SMT) is approximately 66% after one year. With an assumed TFS rate of approximately 82% in the TIPS group, this corresponds to a hazard ratio of 0.48 of the TIPS group compared to the control group (SMT group). The assumption is based on the study by Bureau et al. that analysed 62 patients. The one-year rate of TFS in the TIPS group was 93% (95%CI, 82%–100%) [12]. The TFS probability of the SMT group was assumed according to data from patients with first decompensation with ascites in the INCA trial (unpublished data [24] and, the data provided by Balcar et al. that report1-year TFS in patients with LVP [14]. The effect of TIPS implantation will be assessed by a test at two-sided significance level of 5% and by estimation of the hazard ratio with corresponding asymptotic two-sided 95% confidence interval. The null hypothesis is rejected if the confidence interval does not contain one. Under the above assumptions, the study is planned to detect a difference between the experimental intervention (TIPS group) and the control group (SMT group) with a power of 80%, which requires a total number of 57 events to be observed. The required number of patients to be randomised to observe this amount of events depends on the length of follow-up. With a recruitment period of three years, an additional follow-up period after the end of recruitment of two years, it can be safely assumed that a sufficient number of events will have been observed by the end of the trial if 116 patients are available for analysis (software used, e.g. n Query Advisor 8.3). Furthermore, the exponential drop-out rate is assumed to be 0.01. Therefore, 134 patients will be randomised. Before the end of the planned recruitment phase, a blinded assessment of the TFS rate (both treatments combined) will be performed. If the TFS rate appears to be higher than anticipated, the recruitment phase will be extended, and the required number of patients will be calculated anew under the amended assumptions. Irrespective of this sample size amendment, the analysis will be conducted after the observation of 57 events as planned, so no alpha adjustment is necessary.

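### The adverse-event analysis codes the end of documentation as a competing event rather than as censoring, so late-occurring AE types are understated at the maximum observation time

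*Protocol article*

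**What the plan says.** The statistical methods section {20a} of the protocol article says that the probability of AEs, by MedDRA preferred term (PT) and system organ class (SOC), "will be estimated by the Aalen-Johansen estimator". The variable is "the time from randomisation to the first occurrence of the specific type of AE". For patients who do not have that AE, the rule reads: "end of the documentation period or death, whatever occurs first, will enter the analysis and will be treated as a competing event". No censoring category is named. The summary tables are produced by "showing the cumulative incidences at the maximum observation time".

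The length of documentation is fixed elsewhere. The section on adverse event reporting {22} has AEs recorded "starting from the date of ICF signature and until end of the study". The footnote to Table 3 gives "EOS = end of the entire study is defined as 12 months after randomisation of the last patient". The recruitment section {15} plans 36 months of accrual. The sample size section {14} describes the calendar differently: "With a recruitment period of three years, an additional follow-up period after the end of recruitment of two years".

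**The concern.** A competing event is one after which the event of interest can no longer occur. Death qualifies. The end of documentation does not: a patient who is alive and AE-free at study end may still have the AE later, and is simply no longer observed. That is administrative censoring.

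The protocol draws this line correctly for its paracentesis endpoint. Estimand 2 and Table 4 list only transplantation and death as competing, not the end of observation.

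If every AE-free patient leaves through a competing event, nobody is censored and the estimator has nothing to correct for. The table entry would be labelled as a cumulative incidence at the longest follow-up, but would be a proportion averaged over patients observed for very different lengths of time. Several AEs in Table 5 can arise throughout follow-up, for example hepatic encephalopathy, acute kidney injury, infection and TIPS dysfunction. These are harms that a reader would weigh against any survival benefit.

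**Working it through.** **Inputs from the protocol article.** One-year transplantation-free survival (TFS) is 66% (SMT) and 82% (TIPS), from {14}. Accrual lasts 3 years, from {14} and {15}. Follow-up after the last randomisation is 1 year (Table 3 footnote), giving 1-4 years per patient, or 2 years ({14}), giving 2-5 years.

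**Assumptions.** The plan states no AE incidence, so the AE hazard *h* is assumed constant, at 0.1 to 0.3 per year, and at first equal in both arms. Accrual is uniform. The exponential TFS hazard *d* stands in for the death hazard. TFS also counts transplantation, so a lower true death hazard would leave more patients at the end of documentation and enlarge the bias.

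**Step 1: the plan's own figure.** *d*(SMT) = -ln 0.66 = 0.4155 per year and *d*(TIPS) = -ln 0.82 = 0.1985 per year. Their ratio is 0.4776, which agrees with the stated hazard ratio of 0.48.

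**Step 2: what the rule estimates.** Without censoring, the Aalen-Johansen estimate at the last time point equals the number of patients with the AE divided by the number of patients. A simulation of 67 patients per arm (3,000 runs, *h* = 0.2) gave agreement to within rounding error.

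**Step 3: formulas.** With censoring at the end of documentation, the target at maximum follow-up *b* is

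F(b) = h/(h+d) × [1 − exp(−(h+d)b)].

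Under the plan's rule, the expected value is the mean of F(u) for u uniform on (a, b):

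h/(h+d) × {1 − [exp(−(h+d)a) − exp(−(h+d)b)] / [(h+d)(b−a)]}.

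F increases with time, so its mean over follow-up cannot exceed F(b). The direction is downwards, or nil when no AEs of that type occur after time a.

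**Step 4: one case in full.** TIPS, h = 0.3, follow-up 1-4 years: h+d = 0.4985 and h/(h+d) = 0.6019. Censored: 0.6019 × (1 − 0.1362) = 52.0%. As written: 0.6019 × [1 − (0.6075 − 0.1362)/(3 × 0.4985)] = 0.6019 × (1 − 0.3152) = 41.2%. The loss is 10.8 points, or 20.7%.

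**Step 5: the range, equal AE hazards.**

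| Follow-up | h per year | TIPS: censored → as written | SMT: censored → as written |
|---|---|---|---|
| 1-4 years | 0.1 | 23.4% → 17.1% (−26.9%) | 16.9% → 13.5% (−20.2%) |
| 1-4 years | 0.2 | 40.0% → 30.5% (−23.7%) | 29.7% → 24.5% (−17.6%) |
| 1-4 years | 0.3 | 52.0% → 41.2% (−20.7%) | 39.5% → 33.5% (−15.3%) |
| 2-5 years | 0.1 | 26.0% → 21.3% (−17.9%) | 17.9% → 15.9% (−11.4%) |
| 2-5 years | 0.2 | 43.3% → 37.0% (−14.7%) | 31.0% → 28.2% (−9.1%) |
| 2-5 years | 0.3 | 55.2% → 48.7% (−11.9%) | 40.8% → 37.8% (−7.2%) |

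Brackets give the relative change. Over a wider range of hazards (0.02 to 2 per year, 1-4 years) it runs from about −30% to −1.7% in TIPS and from about −23% to −1.2% in SMT. Very frequent AEs are little affected, because most patients have them early.

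**Step 6: unequal AE hazards.** With 0.5 (TIPS) and 0.2 (SMT) per year and 1-4 years, the relative bias is −15.7% against −17.6%, while TIPS still loses more in absolute terms (10.5 against 5.2 points). With 1.0 and 0.2 and 2-5 years, the absolute loss reverses as well: 1.8 points in TIPS against 2.8 in SMT.

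**The case against.** The strongest case against the point is that these are descriptive tables. No hypothesis test, and neither power nor alpha, depends on them. A crude proportion is a usable safety summary in its own right, and {20a} also gives total follow-up days and AEs per follow-up day. The curves are to be shown over time, and up to 12 months the coding does almost no harm: nobody reaches the administrative end before then, and the assumed drop-out rate is only 0.01. All of this stands and limits the importance of the point. It does not rescue the rule. The exposure-adjusted rate is described only for AEs in total, not by PT or SOC, and the summary tables report the latest time, where the distortion is greatest.

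Two stronger readings are tempting, and the documents support neither.

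- A reader might infer that every cumulative incidence is biased. AE types confined to the period before the first administrative end, such as the procedural complications in Table 5, are not.
- A reader might infer that the rule systematically hides harm from TIPS. A larger loss in the TIPS arm requires both the planned survival benefit and similar AE hazards, and Step 6 shows that the ordering can reverse. In the equal-hazard examples the arm difference does shrink (at 0.3 per year and 1-4 years, from 12.5 to 7.7 points), but that difference arises only because TIPS patients live longer and stay at risk longer; no excess hazard is concealed. The safety set is also analysed by treatment received, and SMT patients may receive TIPS under {11b}, so the planning hazards of the randomised arms describe the safety groups only approximately.

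**Conclusion.** The rule is wrong as written. It is a stated rule and not a detail left open, so an analysis plan that followed it would inherit the error. The value reported at the maximum observation time is a crude proportion over unequal follow-up, and is biased downwards for any AE type that can occur after the first patients reach their administrative end.

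Under the assumptions listed (constant and equal AE hazards of 0.1-0.3 per year, uniform accrual, TFS hazard as proxy for death), the relative understatement is about 21-27% in TIPS and 15-20% in SMT with 1-4 years of follow-up, and about 12-18% and 7-11% with 2-5 years. The documents do not settle which arm is affected more. The primary analysis is untouched.

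**What to change.** Replace the sentence in {20a} with a rule of this kind: death before the AE is a competing event; patients who are alive and AE-free at the end of documentation, or at drop-out, are censored at that date. Report the Aalen-Johansen cumulative incidence by group at a fixed time that every patient can reach, such as 12 months, and show later times only with the numbers at risk. If crude proportions are wanted as well, call them that and give the length of follow-up beside them.

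Reconcile the one-year follow-up after the last randomisation in the Table 3 footnote with the two years in {14}, since this sets the range of observation.

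The correction to the AE rule costs one sentence and one status code in the analysis program. It needs no additional data and places no burden on patients.

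### Adverse-event incidences are tabulated only at the maximum observation time, a horizon the protocol does not fix and that lies years after scheduled assessments end; 12 months should be the main entry

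*Protocol article*

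**What the plan says.** All references are to the protocol article.

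- **Statistical methods {20a}.** The probability of each AE type, by preferred term and by system organ class, "will be estimated by the Aalen-Johansen estimator", counting from randomisation to first occurrence. For patients without that AE, the time to "end of the documentation period or death, whatever occurs first, will enter the analysis and will be treated as a competing event". The table entry is then fixed: "The results will be displayed in summary tables by showing the cumulative incidences at the maximum observation time". The section adds: "Incidences of AEs will be calculated with 95% confidence intervals". No other time is named for these tables. The same section compares quality of life at months 6 and 12.
- **Participant timeline {13}, Table 3.** Laboratory tests, Doppler ultrasound and the clinical scores row, which includes encephalopathy grading, are last marked at month 12. The six-monthly follow-up column after that marks survival or transplantation status and (S)AEs. A footnote states: "end of the entire study is defined as 12 months after randomisation of the last patient".
- **Sample size {14}.** "With a recruitment period of three years, an additional follow-up period after the end of recruitment of two years" is assumed.
- **Retention {18b}.** "After the first year, phone calls also promote long-term follow-up".
- **Adverse event reporting {22}.** "Adverse events have to be documented in the eCRF starting from the date of ICF signature and until end of the study".

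**The concern.** The time at which AE incidences are tabulated should be the same in both arms, known in advance, and reached under one assessment schedule. The maximum observation time meets none of these conditions. It depends on the earliest-recruited patients who remain under follow-up, so it can fall at different times in the two arms. The document itself gives two values for it. It also falls well after the scheduled assessments that detect several of the events listed in Table 5, such as acute kidney injury, encephalopathy from grade II and TIPS dysfunction. Later ascertainment continues, but less intensively.

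These tables are the harm side of the decision on early TIPS. A reader will take the entry as the probability of the event by a stated time. As planned, the time is unclear. Depending on how end of documentation is coded, the figure is either an estimate from a nearly empty risk set or a proportion that is not the probability at that time.

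**Working it through.** **1. Length of follow-up.** Recruitment lasts 3 years.
- Table 3 footnote: study ends 1 year after the last randomisation. Individual follow-up is 1 to 4 years (3 + 1).
- Sample size section: 2 further years. Individual follow-up is 2 to 5 years (3 + 2).

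The sample size section also allows recruitment to be extended and ties the analysis to 57 events, so the maximum is not settled by either figure.

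**2. The plan's own figures.** One-year transplantation-free survival (TFS) of 66% and 82% gives HR = ln 0.82 / ln 0.66 = 0.478 (stated: 0.48). Schoenfeld events = 4(1.960 + 0.842)² / (ln 0.478)² = 57.5 (stated: 57). The survival inputs are therefore the plan's own. The document states no number at risk at the end.

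**3. Expected patients still followed.** Assumptions: 134/2 = 67 per arm, uniform recruitment over 3 years, exponential TFS, no drop-out, maximum T years. TFS is a proxy for being under observation. The AE rule names only death and end of documentation, and patients who have had the AE also leave the risk set.

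N(t) = 67 × min(1, (T − t)/3) × S^t, with S = 0.66 (SMT) or 0.82 (TIPS).

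- t = 1: 67 × 0.66 = 44.2; 67 × 0.82 = 54.9. Nobody has reached end of study under either rule.
- T = 4, t = 3: 67 × (1/3) × 0.66³ = 6.4; 67 × (1/3) × 0.82³ = 12.3.
- T = 4, three months before the end: 1.2 and 2.7. One month before: 0.4 and 0.9.
- T = 5, one month before the end: 0.2 and 0.7.

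**4. What the entry estimates under each coding.** The document gives no AE rates. Assume a constant AE hazard λ = −ln(1 − p), with p = 10% or 30% at one year in the absence of competing events. Let μ = −ln S and s = λ + μ.

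- True cumulative incidence at t: (λ/s)(1 − e^(−st)).
- As worded (nobody censored), the Aalen-Johansen value at the maximum equals the number with the AE divided by all patients in the arm. Its expectation is (λ/s)[1 − (e^(−sF) − e^(−sT)) / (3s)], with F the minimum follow-up in years.

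TIPS, p = 10%, F = 1, T = 4: λ = 0.1054, μ = 0.1985, s = 0.3038, λ/s = 0.3468, e^(−s) = 0.7380, e^(−4s) = 0.2966.
- True at 4 years: 0.3468 × 0.7034 = 0.244.
- As worded: 0.3468 × [1 − 0.4414/0.9114] = 0.179. Binomial SE = √(0.179 × 0.821/67) = 0.047.
- True at 12 months: 0.3468 × 0.2620 = 0.091.

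Simulation, 2000 trials per scenario, mean (SE):

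| Max. | Arm | p | At 12 months, either coding | True at max. | At max., as worded | At max., censored |
|---|---|---|---|---|---|---|
| 4 y | SMT | 10% | 0.083 (0.033) | 0.177 | 0.141 (0.043) | 0.174 (0.063) |
| 4 y | SMT | 30% | 0.248 (0.053) | 0.441 | 0.379 (0.058) | 0.434 (0.073) |
| 4 y | TIPS | 10% | 0.090 (0.035) | 0.244 | 0.179 (0.047) | 0.241 (0.083) |
| 4 y | TIPS | 30% | 0.275 (0.055) | 0.573 | 0.463 (0.061) | 0.563 (0.084) |
| 5 y | SMT | 10% | 0.083 (0.035) | 0.187 | 0.166 (0.046) | 0.185 (0.055) |
| 5 y | SMT | 30% | 0.247 (0.052) | 0.452 | 0.423 (0.061) | 0.446 (0.066) |
| 5 y | TIPS | 10% | 0.089 (0.034) | 0.271 | 0.223 (0.050) | 0.268 (0.072) |
| 5 y | TIPS | 30% | 0.273 (0.054) | 0.602 | 0.539 (0.061) | 0.594 (0.073) |

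As worded, the entry falls short of the true value by 0.021 (5 y, SMT, 10%) to 0.110 (4 y, TIPS, 30%). Under censoring it is close to the truth, but its SE is larger than at 12 months in every row.

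**5. Drop-out before month 12.** This is the only source of difference between the codings at 12 months. The sample size section gives an exponential rate of 0.01 without a time unit. Per year, 67 × (1 − e^(−0.01)) = 0.7 patients per arm; per month, 67 × (1 − e^(−0.12)) = 7.6.

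**The case against.** The strongest reply is that the protocol, as worded, censors nobody. A reader who sees the thin tail might infer that these are the least reliable points on the curves, that one late event causes a large jump, and that the intervals must be very wide. The text does not support that. With end of documentation as a competing event, a late event adds 1/67, about 1.5 points, like any other, and the SE at the maximum is 0.043-0.061 against 0.033-0.055 at 12 months. Even under censoring, the mean number still at risk at the last observed AE was about 4 to 14 in the simulation. The relative SE need not be worse than at 12 months either: 0.083/0.241 = 34% against 0.035/0.090 = 39%. This part of the reply stands.

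A reader might also infer that follow-up for harms stops at month 12, or that the arms cannot be compared fairly. Neither follows. AEs are documented to the end of study, and the six-monthly schedule after month 12 is the same in both arms.

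The section also plans AEs per follow-up day and estimates incidence over time. Whole-follow-up incidence is a legitimate summary, and a table limited to 12 months would leave out late events. This is a good reason to keep the whole-follow-up value, but not to make it the only entry.

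**Conclusion.** The point holds as a fault in the choice of horizon. The tabulated time is not fixed (about 4 or about 5 years, possibly different by arm) and lies 3 to 4 years after scheduled laboratory tests, Doppler and encephalopathy grading end.

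The entry has a defect under either coding. As worded, it is a crude proportion over unequal follow-up that understates the probability at the maximum time by about 2 to 11 percentage points in the scenarios tried. Under censoring, the estimate is nearly unbiased, but about one patient or fewer per arm is expected under observation in the last month, and the SE rises to 0.055-0.084.

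The sizes rest on assumed AE probabilities of 10% and 30%, constant hazards, uniform recruitment, no drop-out, and TFS as a proxy for remaining under observation. The conclusion about the horizon does not depend on those figures. The change should be made, but it concerns a descriptive safety table and does not touch the primary analysis.

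**What to change.** In the AE paragraph of section {20a}, replace the table time by 12 months after randomisation, in both arms, with 95% confidence intervals, as the main entry. Keep the whole-follow-up value as an additional descriptive column, labelled with the length of follow-up it covers. Show the full curves with numbers at risk.

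At 12 months every patient has had the same planned visit schedule from month 1 on, nobody has reached end of study, and the result is the same whether end of documentation is censored or treated as a competing event, apart from drop-out. The change therefore does not have to wait for the coding to be settled. The end-of-study definition in Table 3 and the follow-up period in the sample size section should be reconciled, so that the extra column has a defined length.

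The cost is one sentence and a slightly larger table. Late events do not enter the 12-month figure, but remain visible in the extra column and the curves.
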